### Measures

#### Baseline questionnaire

Parent A (the primary caregiver) will complete a baseline questionnaire including infant date of birth, birth weight, birth order, gestation, the type of milk being given, approximate number of feeds during the day and the night, caregiver's date of birth, country of birth, the main language spoken in the home, current marital status and highest level of education completed. Details are also gathered regarding partner date of birth, country of birth and their highest level of education completed. They will also be asked where their infant spends most of the night (parents bed, own cot/bed in other room, own cot/bed in parent's room or 'other') and whether their infant has been diagnosed with or suspected of any major illness.

Parent A will complete the 'doubt' subscale of the Maternal Cognitions about Infant Sleep Questionnaire [25] (see below). Other subscales are not relevant at such a young age. Feelings of parental doubt may already manifest at 2 to 4 weeks of age and such doubts are associated with increased likelihood of infant sleep problems [25]. Parent A will also be asked whether they think they are a relaxed or tense person (0 = relaxed to 10 = tense; Sayers, 2004); being 'tense' (scoring 7 or higher) predicts higher infant irritability at nine weeks of age.

#### Follow up questionnaires

In order to establish the efficacy of this intervention, we are measuring outcomes at infant age four and six months, since most infants 'sleep through the night' by four months of age [58] and no longer require night time feeding to meet their nutritional needs by six months of age. Measurement at these time points will therefore indicate established sleep patterns of these infants.

Both Parent A and Parent B (secondary caregiver) will complete follow up questionnaires at infant age four and six months. Only Parent A will complete an infant behaviour diary and the feeding questions at these time points.

### Primary & secondary outcomes

Our primary outcome is parent report of infant night time sleep problems. Secondary outcomes include parent report of day time sleep problems, infant crying problems and feeding problems. Parents will be asked 'Have any of the following baby behaviours been a problem for you over the last 2 weeks? Daytime sleep (yes/no), Night-time sleep (yes/no), Crying (yes/no)' [59]. If a parent answers 'yes' to any of these, they will rate the severity of the problem on a seven point Likert scale from 1 = 'hardly any problem' to 7 = 'a severe problem' [43].

Parent A will also complete an infant behaviour diary over a 72 hour period, during which they will record whether their infant is sleeping, feeding, awake and content or awake and crying/fussing in 10-minute epochs. This diary has been adapted from the Barr diary which measures such behaviours in 5 minute epochs and has sound psychometric properties [60].

### Parental sleep quality and quantity

Two items have been adapted from the validated Pittsburgh Sleep Quality Index (PSQI) [61] to measure parent perception of sleep quantity and quality: (1) 'Over the last two weeks, how would you rate your own sleep quantity?' with responses of 'Not nearly enough', 'Not quite enough', 'Enough' or 'More than enough' and (2) 'Over the last two weeks, how would you rate your own sleep quality?' with responses 'Not nearly good enough', 'Not quite good enough', 'Good enough' or 'More than good enough'.

Parents will also report how many times and for how long on average they attended their infant for night waking over the past week.

### Postnatal depression

The Edinburgh Postnatal Depression Scale (EPDS) [62] is a validated screen of postnatal depression (PND) [63,64] consisting of 10 items. Clinically significant levels of PND are indicated by scores ≥ 10 and ≥ 9 for mothers and fathers in community samples, respectively.

### Parental cognitions around infant sleep

The 20-item Maternal Cognitions about Infant Sleep Questionnaire (MCISQ) [25] has 5 subscales including: limit setting (ability to resist infant demands), anger (anger, regret and helplessness), doubt (uncertainty regarding ability as a parent), feeding (belief about the importance of feeding to settle and concerns about child going hungry) and safety (concerns about cot death). We have not included the 'feeding' subscale as it is not associated with infant sleep problems [25].

### Parental perception of infant temperament

Parents will rate their infant's temperament on a six point scale: 'Compared to other babies, I think my baby is:' Much easier than average, Easier than average, Average, More difficult than average, Much more difficult than average or cannot say. This single item from the Australian Temperament Project-a longitudinal study of 2000 children-has a moderate correlation with the Australian version of the Revised Infant Temperament Questionnaire [65].

### Sources of alternate help for infant sleep/crying

Parents will be asked if they have received help or advice (professional or otherwise) from outside the program for either their infant's sleep/crying or for their own stress, and if so, how many appointments they attended for each.

### Feeding

Parent A will indicate the type of food being offered to their infant at present (breast milk, formula or a combination of these) [66,67], and if applicable, whether breast feeding has stopped and why, whether their infant's formula has changed at any stage and whether the mother has changed her own diet while breastfeeding. The 6 month questionnaire also asks about timing of introduction and type of solids.

### Caregiver support and self-efficacy

At baseline and follow up, parent A will rate the level of support or help they receive from their partner and family and friends living elsewhere (I get enough help, I don't get enough help, I don't get any help, I don't need any help), and how often they feel they need support or help but can't get it from anyone (very often, often, sometimes, never, I don't need it) (LSAC) [68]. Parent A will rate their efficacy as a parent (from 1 = not very good to 5 = a very good parent) [68].

### Parental use of intervention materials

Intervention parents will be asked which components of the intervention they received or participated in and usefulness of each, on a study-designed scale ('not at all (useful), a little, quite a bit, a great deal'). Intervention parents will also be asked to rate the helpfulness of specific strategies provided in the intervention materials as either helpful or unhelpful.

### Procedures

Throughout the recruitment phase, MCH nurses approached all families of newborn infants at the first home visit and asked permission to pass on to the research team the contact details of families interested in hearing more about the research. The research team contacted interested families to explain the study further and posted a recruitment pack (information statement, consent form and baseline questionnaire) to parent A and an information pack (information statement and consent form) to parent B if requested. Families were randomised upon receipt of their signed consent form and baseline questionnaire.

Families allocated to the usual care group received a letter explaining that they will continue to see their MCH nurse as usual. Those allocated to the Baby Business intervention group were mailed the booklet and DVD.

A member of the study team completes the telephone consultation with intervention group parents one to two weeks after sending the booklet and DVD. Families are then invited to attend a parenting group session when their infant is around 12 weeks of age. Neither the telephone consultation nor the parent group is compulsory, and parents who do not take part in these components will not be removed from the study given that they will already have received most of the program content via the booklet and DVD. Data will be gathered on participation in each component.

In order to minimize study drop-out, we will call parents if they have not returned their follow up questionnaires two weeks after they were mailed to them. If we do not receive the completed questionnaire in the two weeks following this, we will call the parent again and give the parent the option of completing a shortened version of the questionnaire (covering only the main outcome measures of whether infant sleep, crying and feeding are a problem) over the phone.

### Hypotheses

We hypothesise that intervention parents compared to control group parents will, at infant age four and six months, report:

• fewer infant night time sleep problems (primary outcome)

• fewer infant day time sleep problems

• fewer crying problems

• decreased mean infant crying duration and increased mean infant sleep duration/24 hours

• improved parent sleep quality and quantity,

• improved mental health with lower mean EPDS scores and lower proportions of mothers scoring > 10 and fathers scoring > 9 on the EPDS

• less difficult infant temperament,

• fewer visits to healthcare professionals for their infant's sleep and crying and their own wellbeing

• higher rates of breastfeeding, fewer formula changes and fewer dietary changes in breastfeeding mothers

#### Analysis plan

Outcome data at 4 and 6 months will be presented using descriptive statistics. Means and standard deviations will be given for continuous outcomes, as well as medians and inter-quartile ranges where continuous data are skewed. Proportions for categorical data will also be given. The primary outcome comparison will be of the proportion of infants with sleep and cry problems at 4 months between the two trial arms. Logistic regression adjusting for potential confounders identified a priori, and measured at baseline (including child gender and family socioeconomic status), will be used to estimate the treatment effect as an odds ratio and 95% confidence interval. Random effects regression models [69,70] will be used for further longitudinal analysis examining trends in treatment response, that is, persistence of sleep and cry problems from baseline to 4 and 6 months post intervention. Similar analysis will be carried out for each of the categorical outcomes. We will also compare mean scores for continuous outcomes at the primary endpoint of 4 months (e.g. sleep duration/24 hours) between the two trial arms using t tests, as well as linear regression adjusting for potential confounders. The study sample size is sufficient to enable the use of such techniques when the outcome data are skewed [71], and empirical bootstrap estimates will be examined to confirm the validity of the inferences made. Trends in treatment response will again be examined from baseline to 4 and 6 months post intervention using random effects regression models. All analyses will be conducted on the basis of intention to treat. The frequency and patterns of missing data will be examined and sensitivity analyses will be performed comparing the results of analyses restricted to families with complete data and analyses where missing data are imputed using a conservative approach [72].

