**Methods/Design:**

750 families from four Local Government Areas in Melbourne, Australia have been randomised to receive the *Baby Business *program (intervention group) or usual care (control group) offered by health services. The *Baby Business *program provides parents with information about infant sleep and crying via a DVD and booklet (mailed soon after birth), telephone consultation (at infant age 6-8 weeks) and parent group session (at infant age 12 weeks). All English speaking parents of healthy newborn infants born at > 32 weeks gestation and referred by their maternal and child health nurse at their first post partum home visit (day 7-10 postpartum), are eligible. The primary outcome is parent report of infant night time sleep as a problem at four months of age and secondary outcomes include parent report of infant daytime sleep or crying as a problem, mean duration of infant sleep and crying/24 hours, parental depression symptoms, parent sleep quality and quantity and health service use. Data will be collected at two weeks (baseline), four months and six months of age. An economic evaluation using a cost-consequences approach will, from a societal perspective, compare costs and health outcomes between the intervention and control groups.

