### Sample Size/Power calculation

In a Victorian survey of 724 mothers, [4] 34% reported sleep problems at mean infant age of 4.6 months (range 3-6 months). In a community survey of Queensland parents [56] 27% reported a problem in their 4-6 month old infants (n = 740). Drawing upon this data, a relative reduction in the prevalence of parent report of an infant sleep problem (sleep problem yes/no) by 30% at infant age four months (i.e. from 30% to 20%) is likely to be clinically significant and to have flow on effects for parent mental health. Assuming this, we aimed to detect a reduction in the proportion of infant sleep problems from 30% to 20% at 4-months with 80% power at the 5% significance level. In a trial that randomises individuals, we required 313 subjects in each arm or a total of 780 families, allowing for a 20% loss to follow up. Due to time and budget restraints, we have been able to recruit 750 families only, giving us 78% power to detect a reduction in the proportion of infant sleep problems from 30% to 20% at 4-months, at the 5% level of significance.

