### Reducing bias

Despite being at risk of response and subjective bias, parental *perceptions *of either a sleep or cry problem (yes/no) is our most important outcome measure, given its relation to increased parental depression symptoms, early weaning and increased risk of Shaken Baby Syndrome. To counteract the disadvantages of using a subjective outcome measure, we are also using a validated behaviour diary to obtain measures of sleep and cry duration. In a previous study of 446 infants, we found that diary data including total crying time and number of bouts of crying/24 hours were significantly increased in parents who reported problem crying in their infant vs. those who did not, whilst sleep duration and number of bouts of sleep/24 hours were significantly reduced in infant's whose parents reported a sleep problem vs. those who did not [5].

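### The Analysis plan's primary comparison (sleep and cry problems) contradicts the night-time sleep primary outcome named in three other sections, and the stated power does not cover it

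*Protocol article*

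**What the plan says.** Three sections of the protocol article name the primary outcome, and they agree on the variable.

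- Abstract, Methods/Design: "The primary outcome is parent report of infant night time sleep as a problem at four months of age".
- Primary & secondary outcomes: "Our primary outcome is parent report of infant night time sleep problems". The next sentence reads "Secondary outcomes include parent report of day time sleep problems, infant crying problems and feeding problems".
- Hypotheses: "fewer infant night time sleep problems (primary outcome" is the first item of a list whose shared stem mentions four and six months.

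The Analysis plan says something else: "The primary outcome comparison will be of the proportion of infants with sleep and cry problems at 4 months".

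Two further sections use other wording. Sample Size/Power calculation plans on "parent report of an infant sleep problem (sleep problem yes/no", with no night-time limit and no crying. Reducing bias says that parental perception of "either a sleep or cry problem (yes/no) is our most important outcome measure".

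The questionnaire asks three separate items: "Daytime sleep (yes/no), Night-time sleep (yes/no), Crying (yes/no". These wordings therefore correspond to different variables in the data set.

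**The concern.** The Analysis plan is the section an analyst would follow, and its sentence does not describe the declared primary outcome. Sleep is no longer restricted to the night, and crying, elsewhere secondary, becomes part of the primary comparison. The phrase can mean two proportions tested in turn, infants with both problems, or infants with either. No rule chooses among these, and no multiplicity rule is given for the case of two tests.

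The ambiguity matters more here than in a blinded trial. Families know their allocation (Randomisation), and the outcome is a subjective report, as Reducing bias concedes. A fixed endpoint is then a main protection against a definition being settled after the results are seen. The power statement is also tied to one endpoint and one test, so it holds for some readings and not for others.

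**Working it through.** **Inputs.** From Sample Size/Power calculation: 30% against 20%, 80% power, 5% level (two-sided assumed, since sidedness is not stated), 313 per arm, 20% loss, 750 recruited, 78% power. From Crying in infants: crying reported as a problem by 14–28% of parents. Assumed: sleep problem rate p = 0.30; correlation φ between sleep and crying problems of 0 to 0.4; crying effects as stated below.

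**1. The plan's own figures.**

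n = [1.960·√(2·0.25·0.75) + 0.8416·√(0.3·0.7 + 0.2·0.8)]² / 0.10² = (1.2002 + 0.5119)² / 0.01 = 293.15, so 294 per arm.

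With continuity correction: (293.15/4)·[1 + √(1 + 4/(293.15·0.10))]² = 312.8, so 313 per arm, as stated. Allowing for loss, 626/0.8 = 783, close to the stated 780.

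Power at 750·0.8/2 = 300 per arm:
- uncorrected: z = (0.10 − 0.0693)/0.0351 = 0.874, power 80.9%;
- corrected (subtract 1/300): z = 0.779, power 78.2%, matching the stated 78%.

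The arithmetic is sound for one binary endpoint and one test at 5%.

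**2. Two separate tests at 5%, success on either.** Familywise error is at most 1 − 0.95² = 9.75% (independent tests; lower if they are positively correlated). Splitting alpha to 2.5% each reduces uncorrected power for sleep from 80.9% to 72.3%, and 375 analysed per arm would be needed for 80% power (continuity-corrected).

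If both tests must succeed and crying also falls by one third, the power for crying alone is 43% (14% base rate) to 77% (28%). Joint power is then at most 43–77%, and 35–63% if the tests are independent.

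**3. Composites.** P(both) = pq + φ·√[p(1−p)q(1−q)] and P(either) = p + q − P(both). Example with q = 0.14 and φ = 0.4: both = 0.042 + 0.4·0.1590 = 0.106; either = 0.30 + 0.14 − 0.106 = 0.334.

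Power in per cent, 300 per arm, uncorrected, under three effect assumptions: (A) the composite itself falls by one third; (B) sleep and crying each fall by one third; (C) sleep falls from 30% to 20% and crying does not change.

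| Crying, φ | Control rate: both | Both: A / B / C | Control rate: either | Either: A / B / C |
|---|---|---|---|---|
| 14%, 0 | 4.2% | 15.2 / 38.4 / 15.2 | 39.8% | 93.4 / 89.4 / 59.6 |
| 14%, 0.4 | 10.6% | 33.0 / 42.5 / 15.0 | 33.4% | 86.3 / 82.7 / 55.3 |
| 28%, 0 | 8.4% | 26.9 / 66.9 / 26.9 | 49.6% | 98.5 / 95.5 / 42.4 |
| 28%, 0.4 | 16.6% | 50.2 / 67.2 / 26.4 | 41.4% | 94.6 / 90.4 / 34.1 |

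So *both* gives about 15–67%. *Either* gives about 83–99% under A or B and about 34–60% under C. The comparator is 80.9%.

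**4. Night-time rate below 30%.** The documents give no separate night-time rate. If it were lower, with the same one-third reduction, uncorrected power would be 71% at a control rate of 25% and 59% at 20%.

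**The case against.** The strongest reply is that the document does have a primary outcome. Every place that names it as such says night-time sleep, the power calculation uses one sleep endpoint and one test, and a single sentence departs from this. The sentence may be loose drafting for two proportions reported in turn, since the Analysis plan later promises similar analyses for the other categorical outcomes. On that view the both-composite, which gives the lowest power, is the least likely reading. This stands as far as it goes: the protocol is not without a confirmatory test, and the low power figures are not a forecast. But the departing sentence is the one that specifies the primary comparison, so the conflict has to be removed in the text.

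A reader might infer more than the documents support:

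- *A rival primary outcome in Reducing bias.* That section defends parental perception as a type of measure alongside the diary. It says most important, not primary.
- *Four and six months as co-primary.* The Abstract, the sample-size section and the Analysis plan all point to four months. The six-month mention in the Hypotheses belongs to a stem shared by the whole list, so an error inflation over two time points would describe a plan that is not there.
- *Two reporters as a contradiction.* Both parents complete follow-up questionnaires, but which answer counts can be settled in the full protocol or SAP, which is not shown.
- *The 30% as an any-sleep-problem rate.* The text says only sleep problem. What the two cited surveys asked cannot be seen here.
- *Power is always lost.* The either-composite gains power if crying also falls.

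**Conclusion.** The Analysis plan sentence is wrong as written: it contradicts the primary outcome in the Abstract, the outcomes section and the Hypotheses, and it does not define what it would test. The sample-size arithmetic is correct, but it supports only a single sleep endpoint tested once at 5%. Under the other readings, power runs from about 15% to about 99%, or familywise error reaches up to 9.75%. These ranges rest on assumed correlation and crying effects and on a 30% sleep rate. They show that the stated 78% cannot be carried over to the other readings; they do not show that the trial is underpowered for its declared outcome. For that outcome the 78% stands if the 30% to 20% assumption applies to the night-time item.

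**What to change.** Make these changes before any between-arm analysis. Allocation is already known to families and follow-up was under way when the article was written, so that is the deadline that matters.

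1. In the Analysis plan, replace the sentence with: *The primary comparison is the proportion of infants with a parent-reported night-time sleep problem (yes/no) at 4 months.*
2. State there that crying, daytime sleep and the 6-month results are secondary.
3. Align the wording in Sample Size/Power calculation, Reducing bias and Hypotheses with that definition.
4. In Sample Size/Power calculation, say that the 30% to 20% assumption is applied to the night-time item, and show power for lower night-time rates as a stated assumption (uncorrected, about 71% at 25% and 59% at 20%).
5. If sleep and crying are both meant to be primary, define the rule (either test, both tests, or a named composite), state how alpha is controlled, and restate the power.

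Items 1 to 4 are edits to text plus a short power table. They need no new participants, data or measurements. Item 5 would also mean accepting a different power, since recruitment is complete.

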#### Economic evaluation

A cost-consequences analysis will be conducted from a societal perspective. Costs and outcomes will be taken into account and valued in the analysis regardless of who bears the costs, who benefits or who provides the resources. The incremental costs of the intervention (the difference of costs accrued in the intervention group and costs accrued in the control group) will be compared to a range of the incremental primary and secondary outcomes. Both costs of delivering the intervention and costs of families' use of health and other services outside of the study will be considered in economics costing.

The economic evaluation will draw a comprehensive picture of the costs and consequences of the intervention and assist policy makers to make appropriate decisions on resource allocation to such interventions and determine the cost-effectiveness of nationwide roll-out.

